### Power calculation

Based on a dynamic Bayesian prevalence estimate, the successful surveillance strategy is expected to test up to 1000 saliva samples per day in order to generate 2- to 5-week predictions on critical care capacity and other relevant health care parameters in the Rhein-Neckar [22]. Each studied strategy should therefore be able to estimate SARS-CoV-2 prevalence with sufficient accuracy. In May 2020, the 4-week cumulative SARS-CoV-2 prevalence estimated by passive monitoring in the Rhein-Neckar District was around 0.25%. Assuming an equally high prevalence of asymptomatic SARS-CoV-2 carriers, the overall prevalence of asymptomatic and symptomatic carriers was approximately 0.5%. A similar prevalence is assumed for future waves.

Strategy A1 is designed to directly reflect the pandemic events using a purely random sample. With a total of 2500 saliva samples, this strategy is able to detect an overall SARS-CoV-2 prevalence of 0.5% with an accuracy of ±0.35% and a power of 95%; a prevalence of 0.2% would be detected with an accuracy of ±0.25% and a power of 93% (confidence interval according to Agresti-Coull) [23]. Assuming a higher SARS-CoV-2 prevalence within families or households of an infected individual, strategy A2 is expected to detect this higher rate accordingly. Given the upstream pre-screening mechanisms and resulting filter effects in strategies B1 and B2, the resulting detection rates related to these strategies should also differ accordingly.

Sample sizes are therefore designed to yield 2500 saliva samples available for analysis in each study arm. The catchment area of the study (i.e., Rhein-Neckar District plus Heidelberg) has approximately 700,000 inhabitants. To ensure sufficient precision of the measured estimates, a total net case number of 1.4% of the target population (i.e., 0.35% per study arm) is targeted. Based on assumptions on participation rates as well as the sensitivity and specificity of the pre-screening tool, the following gross sample sizes are needed for each strategy:

For strategy A1, a response rate of 50% is assumed after one-time prompting, warranting a gross sample of at least 5000 addresses per batch; for strategy A2, an average household size of two with a response rate of 50% after prompting is assumed, warranting a gross sample of at least 2500 addresses per batch [24]. For strategy B1, a 50% response to the first letter and a 50% response to prompting is assumed; further, a response rate of 80% is assumed for those participating in the pre-screening with positive screening results. To ensure a total of 2500 tested samples, at least 3125 test kits must be mailed out for this strategy. Assuming the pre-screening tool’s sensitivity at 90% and specificity at 70% and given a SARS-CoV-2 prevalence of 0.5%, at least 10,313 (=3125/0.303) participants have to complete the pre-screening. Further assuming a 50% response to the initial pre-screening tool and a 50% response after prompting warrants a gross sample of at least 13,750 addresses. Similar to above, for strategy B2 an average household size of two members is assumed, which warrants a gross sample of at least 6875 addresses. For the entire trial, a minimum gross sample of 28,125 addresses is required.

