### Randomization process

The total study sample consists of 10,000 participants with each strategy enrolling 2500 randomly selected participants. Participants are identified and sampled by each selected municipality’s population register provided by the respective registration office. Individuals or households are drawn as a stratified sample proportional to population size. For each of two strata (i.e., all municipalities located in the “Rhein-Neckar District” or in the municipality of the city of “Heidelberg”), individuals or households are drawn in three batches of each three continuous weeks.

For the “Rhein-Neckar District” stratum, a two-stage sample design is used for each batch, within which the primary sampling units (PSU) are drawn as synthetic clusters of secondary sampling units (SSU) (i.e., individuals or households). First, 55 PSUs are randomly selected for each batch independently using probability proportional to size sampling. These 55 PSUs are then distributed across the 56 municipalities (i.e., sampling points) in the “Rhein-Neckar District” stratum using the Cox algorithm. This might result in some sampling points to contain several PSUs. Second, disproportional sampling is used to draw the same number of SSUs for each sampled PSU in order to obtain a self-weighted sample of individuals or households [19]. Since sampling points can contain several PSUs, the number of SSUs per sampling point and batch may vary. As the “Heidelberg” stratum consists only of one municipality, selection of individuals or households is carried out in a single-step simple random sampling process.

The net sample size is then translated into a corresponding gross sample under consideration of the expected response rates in each strategy and the sensitivity and specificity of the pre-screening tool applied to strategies B1 and B2 (see below). The gross sample therefore includes a total of 21,739 individuals or households contacted in the “Rhein-Neckar District” and 6386 in the “Heidelberg” stratum. This way a sample of 28,125 individuals or households is drawn and then randomly allocated to the four strategies A1, A2, B1, and B2 in the ratio 5 to 2.5 to 14 to 7 to eventually yield a final study sample of 2500 saliva tests for each strategy.

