### Statistical analyses

The primary analysis will consist of an intent-to-treat (ITT) evaluation. Secondary analysis will include an estimation of the complier average causal effect using standard instrumental variables [20]. Here, the instrumental variable represents the initial random ITT assignment to the four strategies. The effects on continuous primary and secondary endpoints (e.g., cost per fully screened person, cost per confirmed positive case, cost per asymptomatic case, precision of prevalence) are measured using standard ordinary least square regression. For the effects on binary endpoints, we will use the modified Poisson model [21]. Effects on ordinal categorical endpoints (e.g., participant satisfaction measured on a Likert scale) are measured using an ordered logistic regression. All analyses will be adjusted for clustering of standard errors at the level of the randomization unit (i.e., municipalities). Primary analyses will not account for any baseline covariates; secondary analyses will account for the baseline covariates of age and sex.

In order to comprehensively identify the most cost-effective surveillance strategy, the aforementioned ITT analysis is complemented by a cost-effectiveness analysis evaluating the cost-effectiveness of the four surveillance strategies in relation to the status quo of having only passive surveillance. The cost-effectiveness analysis and underlying micro-costing study adopt a health system perspective to account for all costs incurred at the level of the health system, including the economic costs of all resources consumed in relation to the implementation and maintenance of the four active surveillance strategies, as well as the cost of the comparator (i.e., the passive surveillance system). All costs are measured as continuous variables for each individual. To determine the cost-effectiveness of each of the four surveillance strategies, costs and effects (measured as the number of cases detected) will be set into relation to those of the status quo. Incremental cost-effectiveness ratios (ICERs) are computed for each surveillance strategy in relation to the status quo. The strategy with the lowest ICER is considered as most cost-effective and will then be further appraised in conjunction with information on the prognostic models (described below) to orient decision making on the choice of the most suitable surveillance strategy to be implemented in routine practice.

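### The A1 accuracy figures assume 2,500 independent observations, which matches neither the two-stage sampling nor the planned clustering by municipality

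*Protocol article*

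**What the plan says.** Three sections of the protocol article bear on this.

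- **Power calculation.** "Strategy A1 is designed to directly reflect the pandemic events using a purely random sample". For 2,500 samples and a prevalence of one half of one percent, the claim is an estimate "with an accuracy of ±0.35% and a power of 95" percent. For the lower planning value the article states that "a prevalence of 0.2% would be detected with an accuracy of ±0.25% and a power of 93" percent. The interval method is given as "confidence interval according to Agresti-Coull". No design effect, ICC or effective sample size appears. The gross-sample steps that follow allow for response, household size and pre-screening, but not for clustering.
- **Randomization process.** Outside Heidelberg, the article states that "a two-stage sample design is used for each batch, within which the primary sampling units (PSU) are drawn as synthetic clusters"; each cluster is made up of persons or households, and there are 55 such units (PSUs) per batch and three batches. Heidelberg is a separate stratum with a simple random sample. The gross sample is 21,739 addresses in the district and 6,386 in Heidelberg.
- **Statistical analyses.** "All analyses will be adjusted for clustering of standard errors at the level of the randomization unit (i.e., municipalities".

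Study outcomes lists the precision of the detection rate, expressed as its confidence interval, among the primary outcomes. The text on the four strategies makes A1 the reference against which the bias of the other three is judged.

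**The concern.** The sample-size section, the sampling section and the analysis section describe three different variance structures for the same estimate: independent observations, a stratified sample clustered in one stratum, and clustering by municipality throughout. A1 is the only arm with a numerical accuracy target, and it serves as the yardstick for the others. If its interval is computed as the analysis section says, its width need not resemble what the sample-size section promises. A reader comparing the two could not tell whether a wider interval reflects bad luck, the sampling, or the choice of cluster.

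**Working it through.** **1. Reproducing the stated figures.** Inputs from Power calculation: n = 2,500; prevalence p = 0.5% or 0.2%; Agresti-Coull interval. The confidence level is not given; two-sided 95% (z = 1.96) is assumed. For X cases:

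ñ = n + z², p̃ = (X + z²/2)/ñ, half-width h = z·√(p̃(1 − p̃)/ñ).

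Assurance is P(h ≤ stated accuracy) with X ~ Binomial(n, p).

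- p = 0.5%: with X = 18, ñ = 2503.84, p̃ = 19.92/2503.84 = 0.00796 and h = 0.348 points; with X = 19, h = 0.357. P(X ≤ 18) = **94.86%**, stated as 95%.
- p = 0.2%: with X = 8, h = 0.246 points; with X = 9, 0.258. P(X ≤ 8) = **93.21%**, stated as 93%.

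Other readings of the word power do not match both figures: interval coverage gives 95.5% and 96.2%, and the chance that the estimate lies within the stated accuracy gives 98.9% and 99.5%. The stated figures are therefore simple-random-sample assurances.

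**2. Effect of a design effect (deff).** Assurance of ±0.35 points at 0.5% prevalence, computed in two ways: (a) exact binomial on n = 2,500/deff; (b) beta-binomial case counts with variance inflated by deff, and the interval computed on the effective n.

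| deff | effective n | (a) | (b) |
|---|---|---|---|
| 1.00 | 2500 | 94.9% | 94.9% |
| 1.03 | 2427 | 93.2% | 91.3% |
| 1.05 | 2381 | 90.4% | 91.1% |
| 1.10 | 2273 | 82.7% | 85.9% |
| 1.15 | 2174 | 79.4% | 79.3% |
| 1.20 | 2083 | 75.1% | 71.3% |

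Case counts are whole numbers, so the assurance moves in steps. It still rounds to 95% at deff 1.005 under (a) (95.05%) and at 1.010 under (b) (94.8%). Just above those points it drops to about 92%. The 93% figure at 0.2% prevalence holds at 1.01 but not at 1.02 under (a), and up to about 1.026 under (b).

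**3. Which design effect applies.** The article gives no ICC; 0.0005 to 0.002 is assumed. Equal response in the two strata is also assumed, so A1 splits as the gross sample does:

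- Heidelberg: 2,500 × 6,386/28,125 = 567.6
- District: 2,500 − 567.6 = 1,932.4 (77.3%), which is 1,932.4/165 = 11.7 per PSU over three batches of 55, or 1,932.4/56 = 34.5 per municipality.

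*PSU as cluster, Heidelberg unclustered:* deff = 1 + 0.773 × (11.7 − 1) × ICC = 1 + 8.3 × ICC, which is **1.004 to 1.017**.

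*Municipality as cluster, as written:* deff = 1 + (Σm²/Σm − 1) × ICC.

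- Heidelberg contributes 567.6²/2,500 = 128.9 to Σm²/Σm.
- The 56 district municipalities contribute 56 × 34.5² × (1 + CV²)/2,500 = 26.7 if equal in size (CV 0) and 53.3 if their sizes have CV 1.
- CV 0: 1 + 154.6 × ICC = 1.08 to 1.31. CV 1: 1 + 181.2 × ICC = 1.09 to 1.36. Overall **about 1.08 to 1.36**.

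Heidelberg alone supplies 83% (CV 0) to 71% (CV 1) of the excess over 1. Without its term, the range is 1.01 to 1.05 (CV 0) or 1.03 to 1.11 (CV 1).

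**4. Sensitivity to the ICC.** With PSU clusters and an ICC of 0.005, 0.01 or 0.02, the overall deff is 1.04, 1.08 or 1.17, and the assurance under (b) is 91%, 86% or 79%.

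**The case against.** The strongest case on the other side has five parts.

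- **The arithmetic is right.** Both figures reproduce, so this is a dispute about an assumption. That stands: there is no calculation error to report.
- **Discreteness.** A reader might infer that any design effect above 1 breaks the stated assurance. That is too sharp, as step 2 shows. The two methods also differ by a few points at a given design effect, and method (a) is not even monotone. The table shows the order of the loss, not exact values.
- **The typical interval stays inside the target.** At the expected case count the half-width is 0.296 points at deff 1 and 0.329 at deff 1.2, both below 0.35. With 18 cases it goes from 0.348 to 0.367 at deff 1.1. What is lost is assurance; the interval itself widens modestly.
- **The ICC is assumed.** Within 0.0005 to 0.002 the sampling itself costs little. Stratification, and PSUs spread over nearly all municipalities, could offset part of that. This also stands, and it limits what can be claimed about size.
- **Context.** The phrase about a purely random sample may only contrast A1 with household testing in A2 and the pre-screening filter in the B arms, and the clustering sentence follows the regression models for effects. This is a fair reading of the intent. But the accuracy figures do use independent observations, and the clustering sentence covers all analyses without exception.

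A statistical analysis plan could settle the variance estimator. It would not remove the mismatch, because the article itself states the figure, its basis and a conflicting design.

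**Conclusion.** The point holds in limited form. The A1 accuracy is a simple-random-sample figure, while the article describes a stratified design with two-stage sampling in 77% of the gross sample and an analysis clustered by municipality. There is little reserve: the 95% survives only to a design effect of about 1.01.

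How much is lost depends on the cluster chosen and on an ICC that the article does not give. Under the assumptions in step 3, variance by PSU leaves the assurance between about 91% and 95%. Variance by municipality, applied literally, brings it to about 86% or lower. Most of that larger loss comes from treating Heidelberg as one cluster, although it is its own stratum with a simple random sample, so differences between Heidelberg and the district are not sampling error of the A1 estimate. Municipalities are also not what is allocated to strategies; the Randomization process section allocates individuals or households.

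A reader might conclude that A1 is too small. The documents do not support that: no ICC is given, and with the variance that fits the sampling the loss is small over the assumed range.

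**What to change.** Three changes, none of which touches the sample size (Trial status reports recruitment complete on December 22, 2020):

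1. In Power calculation, replace the description of A1 as purely random by the actual design: two strata, two-stage in the district, simple random sampling in Heidelberg.
2. Restate the A1 accuracy over a range of design effects, for example 1.00 to 1.20, and label the single 95% and 93% figures as holding for independent observations.
3. In Statistical analyses, specify that the A1 prevalence interval is design-based, with two strata, the PSU as cluster in the district and no clustering in Heidelberg, and exempt it from the rule on clustering by municipality.

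The cost is a slightly less favourable stated figure and one line on variance estimation. The third change requires the PSU identifier in the analysis data set.

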## Discussion

Once completed, the *CoV-Surv Study* is expected to identify the most effective, acceptable, and optimal surveillance strategy from multiple scientific perspectives, in order to ensure that the most promising strategy is then to be converted into a routine system as needed. This routine system should be scalable to up to 1000 saliva samples per day to allow reliable predictability during the course of a SARS-CoV-2 wave. For its long-term application, meaning once the SARS-CoV-2 pandemic should be successfully controlled and no longer poses an imminent public health risk, the routine system resulting from the *CoV-Surv Study* is further expected to become a stand-by surveillance method that can be quickly reactivated any time in the event of new pandemic threats. As surveillance is based on RT-LAMP testing of biological samples, this test can be quickly adjusted to any other pathogen of public health concern.

### Active vs. passive surveillance

Systems for active surveillance of the general population will gain more importance in the context of pandemics and related disease prevention efforts. As seen during the current SARS-CoV-2 pandemic, the epidemiological course of an easily transmissible illness follows a typical pattern with an initially low overall prevalence in the general population and a comparatively higher prevalence in local clusters. Even in the absence of so-called super-spreader events, infections continue spreading within the general population and therefore lead to increasing overall prevalence rates over time. While complete lockdowns and similarly drastic interventions are effective in reducing the overall prevalence, these measures should only be used over relatively shortly defined time periods. While milder containment methods (e.g., social distancing, mask-wearing, personal hygiene) effectively prevent local outbreaks, they are usually less effective in preventing infection spread.

While useful in identifying positive cases and tracing their potential contacts, passive surveillance strategies should be supplemented by active routine monitoring of larger population groups based on regular testing. Especially in instances where public life is reopened after a more drastic lockdown, active testing frequencies will need to be increased enormously to prevent larger infection chains or super-spreader events to recur, which otherwise would lead to the next lockdown. The pandemic parameters derived from such active surveillance with routine population monitoring therefore not only enable a prospective assessment of the short-term course of a pandemic, but also a more targeted and thus more effective use of local and short-term countermeasures.

### Further considerations

An ideal active surveillance strategy would frequently test every single person in order to identify all asymptomatic and symptomatic carriers as early as possible and to fully prevent further spread. Obviously, such an ideal strategy is unrealistic and active surveillance approaches therefore will have to work with time-varying randomized samples. Estimated prevalence rates will therefore differ in their uncertainty depending on sample sizes used. This will have significant implications on pandemics like the current one. Since COVID-19 is a respiratory disease that is transmitted similarly to most seasonal viral diseases, SARS-CoV-2 infection rates are also likely to increase during winter months. This is expected to lead to an increase in symptoms similar to COVID-19 during these so-called flu seasons, which will further require the density and frequency of SARS-CoV-2 tests will have to be increased to maintain active surveillance.

### Trial status

The final protocol version is “Surveillance_Studienprotokoll_03Nov2020_v1_2” from November 3, 2020. Recruitment started November 18, 2020, and has been completed on December 22, 2020. This protocol was published as a structured summary (https://doi.org/10.1186/s13063-020-04982-z).

## Data Availability

The quantitative data will populate the National COVID-19 Research Network (Nationales COVID-19 Forschungsnetzwerk) and become available in an anonymized form to other researchers. The goal of this research network is to combine all SARS-CoV-2-specific data in Germany to allow for additional joint analyses. This includes plans for the establishment of an overarching data structure based on standardized variable definitions. Researchers outside the network will be asked to follow an application process prior to data access. On a case-to-case basis, requested data is then prepared accordingly, anonymized, and made accessible together with the respective variable dictionary.

## Abbreviations

CoV: Coronavirus
COVID-19: Coronavirus disease caused by SARS-CoV-2
ITT: Intent-to-treat
PSU: Primary sampling unit
RNA: Ribonucleic acid
RT-LAMP: Reverse transcriptase loop-mediated isothermal amplification
RT-PCR: Reverse transcriptase-polymerase chain reaction
RT-qPCR: Reverse transcriptase quantitative polymerase chain reaction
SEIHR: Susceptible, exposed, infectious, hospitalized, removed
SARS: Severe acute respiratory syndrome
SARS-CoV-2: Novel coronavirus causing COVID-19
SSU: Secondary sampling unit
